### Sample size

The study aims to enrol 120 patients with a goal of 96 patients completing the induction phase. This is based on registration studies evaluating induction of remission with anti-tumour necrosis factor therapy in Crohn’s disease (chimeric monoclonal antibody cA2 study^29^ and CLASSIC I study^30^). Differences ranging from 24% to 29% were achieved (remission rates in intervention group of 33%–36%; remission rates in placebo group of 4%–12%). In addition, two small controlled trials evaluating FMT in Crohn’s disease reported remission rates in the intervention group of 36% and 44% at weeks 8 and 10, respectively.^23 24^

The predicted proportion of patients achieving a response is 60% in the FMT group and 30% in the control group (estimated delta of 30%), based on a double-sided alpha value of 0.05. This also takes into account 20% attrition in each group, to achieve a non-dropout number of 96 patients completing the induction phase of the study.

### Consent

Written and verbal information on the FMT process and informed consent forms will be provided to each patient by the site investigator prior to the screening visit (online supplemental file 2). Written consent for participation in the study will be obtained at the screening visit prior to the collection of medical information and biospecimens. Clinical data will be collected out to 5 years.

Further written consent will be documented at the time of each procedure consenting to the risks associated with the procedure itself, the administration of FMT or placebo, study medications and anaesthesia.

### Primary and secondary endpoints

The primary and secondary endpoints are detailed in table 1.

**Table 1 T1:** Primary and secondary endpoints

Outcome	Definition	Timepoint
Primary		
Clinical response	CDAI decrease of ≥100 or CDAI<150	Week 8
Secondary		
Clinical remission	CDAI<150	Week 8 and week 52Week 16 and week 60 (for open FMT group)
Endoscopic response	SES-CD reduction by 25% and 50%	Week 8 and 52Week 16 and 60
Endoscopic remission	SES-CD ≤2 or absence of ulcers	Week 8 and week 52Week 16 and 60
Histological remission	The absence of ulcers; the absence of acute inflammation histologically; one of either Geboes Score or Robarts Histology Index	Week 8 and 52Week 16 and 60
Radiological remission	IUS (BWT<3 mm and/or Limberg 0 or 1) or MRI (wall thickness<4 mm and no or minimal wall enhancement)	Week 8 and 52Week 16 and 60
Biochemical response	Normalisation of CRP and faecal calprotectin (<50 µg/g, <100 µg/g, <150 µg/g, <200 µg/g, <250 µg/g	Week 8 and 52Week 16 and 60
Time to outcomes	Time taken to achieve clinical response or remission during induction and maintenance phases	Duration of trial
Maintenance of clinical remission	CDAI <150	Weeks 52 or 60
Sustained clinical remission	CDAI <150	Weeks 52 or 60
Steroid-free clinical remission		Weeks 52 or 60
Safety outcomes	Adverse events	Duration of trial
Scientific outcomes	Comparison of genetic, microbiological, metabolic and immunological factors in the responders with the non-responders	Week 8 and 52Week 16 and 60

BWT, bowel wall thickness; CDAI, Crohn’s Disease Activity Index; CRP, C reactive protein; FMT, faecal microbiota transplantation; IUS, intestinal ultrasound; SES-CD, simplified endoscopic activity score for Crohn's disease.

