### Recipient eligibility: induction phase

#### Inclusion criteria

Participants aged 18–70 years with Crohn’s disease proven by endoscopic, histological and/or radiological assessment.Confirmed endoscopic active inflammation (unless isolated small bowel disease that is inaccessible by endoscopy, in which case sonographic inflammation is sufficient) within 6 months of study entry.Crohn’s Disease Activity Index (CDAI) Score of 220–450.At least one of the following:C-reactive protein (CRP)≥5 mg/L.Faecal calprotectin≥100 µg/g.Inflammation on imaging (either intestinal ultrasound (IUS) or Magnetic Resonance Imaging (MRI).Willing and able to attend the study sites for regular endoscopic procedures.

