### Screening processes

#### Participant screening

Referred patients will be assessed by the trial team for eligibility by an initial phone screen evaluating recent endoscopy results, faecal (calprotectin) and serum (CRP) disease activity biomarkers and relevant imaging. The CDAI Score will be calculated, and medical history taken to identify exclusion criteria. Patients who satisfy eligibility criteria will then be invited to the trial hospital sites for a screening visit.

At the study centre screening visit, an extensive medical history will be taken by a physician and clinical nurse. Venepuncture for routine pathology and infections, and a stool assessment for infectious pathogens, antibiotic-resistant bacteria and faecal calprotectin, is undertaken. An IUS is performed to evaluate the presence of sonographic inflammation (defined by a combination of bowel wall thickness ≥3 mm and hyperaemia (Limberg score ≥2). If the location of disease is inaccessible on IUS, or the views are suboptimal, an MRI scan of the small and large bowel is performed. The same modality of imaging will be conducted for the duration of the trial.

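### Biochemical response, radiological remission and endoscopic remission can already be met before the first dose, and no baseline condition is stated for their comparison

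*Protocol article*

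**What the plan says.** **Entry (Inclusion criteria).** Besides a CDAI of 220–450, a patient needs "At least one of the following:C-reactive protein (CRP)≥5 mg/L.Faecal calprotectin≥100 µg/g.Inflammation on imaging", so one of the three is enough. The endoscopic criterion is "Confirmed endoscopic active inflammation (unless isolated small bowel disease that is inaccessible by endoscopy, in which case sonographic inflammation is sufficient", met within 6 months of study entry. It sets no minimum SES-CD and does not ask for ulcers.

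**Screening definition (Participant screening).** Sonographic inflammation is "defined by a combination of bowel wall thickness ≥3 mm and hyperaemia (Limberg score ≥2", so both parts are required.

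**Endpoints (Table 1).**
- Biochemical response: "Normalisation of CRP and faecal calprotectin", with calprotectin cut-offs of <50, <100, <150, <200 and <250 µg/g.
- Radiological remission: "IUS (BWT<3 mm and/or Limberg 0 or 1" on ultrasound, or a wall under 4 mm with no or minimal enhancement on MRI.
- Endoscopic remission: "SES-CD ≤2 or absence of ulcers".
- Endoscopic response: a 25% and a 50% fall in SES-CD.

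**Analysis (Statistical analysis).** The primary analysis population is everyone randomised and dosed. All binary secondary outcomes are compared between arms with a log-link binomial model. Baseline status is not mentioned.

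**The concern.** Three of these endpoints are thresholds at a visit, and the entry rules do not require a patient to be on the wrong side of any particular one. A patient who starts on the right side cannot be moved there by treatment. Counted in both arms, such patients add similar proportions of successes to each and pull the risk ratio, which is the protocol's effect measure, towards 1.

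This matters because the article itself calls the CDAI largely subjective (Strengths and limitations) and looks to the biochemical, sonographic and endoscopic data for objective assessment of disease activity (Discussion). A diluted result on those endpoints could be misread as a failure to confirm a clinical effect. The optimisation phase may add to the problem: diet change and antibiotics come before the week 0 measurements, so some patients may improve on a marker between screening and the first dose.

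**Working it through.** **1. The plan's own figure.** The article gives a sample size only for the primary endpoint. With 60% versus 30%, 2:1 allocation, two-sided 0.05, 80% power and pooled variance (mean rate (0.30 + 2 × 0.60)/3 = 0.50), placebo n = [1.96·√(0.25 × 1.5) + 0.8416·√(0.21 + 0.24/2)]² / 0.30² ≈ 31.5, so 32. FMT is then 64, the total 96, and 96/0.8 = 120. The stated numbers reproduce. No figure is given for the objective secondary endpoints, and the primary endpoint does not have this problem: entry CDAI of at least 220 excludes a CDAI below 150.

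**2. Entry rules against endpoints.**

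| Endpoint | Eligible patient who meets it before treatment |
|---|---|
| Biochemical response | Normal CRP and calprotectin 100–149: below the <150, <200 and <250 cut-offs. Admitted on imaging alone: possibly below all five |
| Radiological remission | Admitted on CRP or calprotectin with no imaging inflammation. If *and/or* is read as *or*, this includes a wall ≥3 mm with Limberg 0–1 |
| Endoscopic remission | Active inflammation without ulcers, whatever the SES-CD |
| Endoscopic response | None, because it is a change score. With baseline SES-CD 0 a percentage fall is undefined and cannot be attained |

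For patients who use the endoscopy exception ("unless isolated small bowel disease that is inaccessible by endoscopy, in which case sonographic inflammation is sufficient"), an SES-CD of 0 with no ulcers at week 0 is possible.

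On ultrasound, the *or* reading of remission is the exact complement of the screening definition, so every patient not inflamed at screening is already in remission. On the *and* reading there is an intermediate state that is neither inflamed nor in remission. The article does not say which is meant.

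**3. Size of the dilution.** Let f be the share already meeting the endpoint, k the probability of keeping it and c the conversion probability among the rest. In each arm:

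p = f·k + (1 − f)·c

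None of f, k or c is in the article. Assumed for illustration: c = 30% FMT and 10% placebo (RR 3.0), and k = 90% in both arms. Power is by exact enumeration of the two-sided score test, at 64/32 with all patients counted, and at 54/27, 48/24 and 38/19 with only those not meeting the endpoint at baseline.

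| f | FMT | Placebo | RR | Power, all | Power, restricted |
|---|---|---|---|---|---|
| 15% | 0.135 + 0.255 = 0.39 | 0.135 + 0.085 = 0.22 | 1.77 | 39% | 56% |
| 25% | 0.225 + 0.225 = 0.45 | 0.225 + 0.075 = 0.30 | 1.50 | 29% | 50% |
| 40% | 0.36 + 0.18 = 0.54 | 0.36 + 0.06 = 0.42 | 1.29 | 20% | 38% |

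Borrowing the primary endpoint's 60% versus 30% as conversion rates, with full retention, gives the same pattern. RR 2.00 becomes 0.68/0.44 = 1.55 at f = 20% and 0.80/0.65 = 1.23 at f = 50%.

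**4. Unequal retention.** Keep c as in the table and let FMT also prevent loss of normal status.

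| Retention, FMT vs placebo | RR at f = 15 / 25 / 40% | Power, all |
|---|---|---|
| 90% vs 70% | 2.05 / 1.80 / 1.59 | 53 / 49 / 46% |
| 90% vs 60% | 2.23 / 2.00 / 1.80 | 60 / 60 / 62% |

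Restricted power stays at 56 / 50 / 38%. The overall RR is a weighted average of the conversion ratio and the retention ratio, so it is diluted whenever the retention ratio is the smaller of the two, as it is here (0.9/0.6 = 1.5 against 3.0). Power need not fall: at 90% versus 60%, counting everyone has more power at every f tested.

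**The case against.** The strongest reply is that denominators for secondary endpoints usually belong in an analysis plan, which is not shown, and that the dosed population is stated for the primary analysis and not expressly for every secondary endpoint. That is fair as to silence. But the breadth of the endpoint definitions is fixed in Table 1, and the text as it stands compares all binary secondary outcomes with no baseline condition.

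Second, normalisation can be read as a move from abnormal to normal, which would exclude patients already normal. That reading is open for the biochemical row. It does not help the two remission rows, which are states.

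Third, the share in remission among all patients is a legitimate quantity, because it includes prevention of worsening. Equal retention is not obvious in patients with CDAI 220–450, some of whom are tapering steroids. This stands, and is why the all-patient result should be kept.

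Fourth, excluding patients already in remission makes no sense at weeks 52/60, where the question after re-randomisation is whether remission is kept. This also stands.

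A reader might infer more: that every endoscopic endpoint can be met at baseline, that restricting always gains power, or that the objective results are certain to be masked. The documents support none of these. Endoscopic response is a change score, the power comparison reverses in the second unequal-retention scenario, and the share meeting each endpoint at baseline is not given. Patients admitted under the endoscopy exception must have sonographic inflammation, so on the screening definition they are not already in ultrasound remission.

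**Conclusion.** The point holds for biochemical response, radiological remission and endoscopic remission at week 8: the entry rules allow each to be met before treatment, and no baseline condition is stated. Endoscopic response has a narrower defect, at baseline SES-CD 0 only.

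The risk ratio is diluted in every case tested, from 3.0 to between 1.29 and 2.23 depending on the baseline share (15–40%) and on retention. These sizes are illustrative, since baseline shares, conversion and retention are all assumed. The loss of power depends on similar retention in the two arms and is not assured.

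The primary CDAI endpoint is unaffected, and type I error is not inflated. This is a correction that should be made to the secondary endpoints, not a threat to the trial's main result.

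**What to change.** **Week 8 induction comparison**
- Analyse biochemical response, radiological remission and endoscopic remission each in patients who do not meet it at the baseline assessment made before the first dose. Under Table 2 that is week 0 for CRP, calprotectin and SES-CD, and week −3 for imaging.
- Analyse SES-CD reduction only where baseline SES-CD is above 0.
- Report the all-patient result as supportive, or adjust it for baseline status.

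**Table 1 wording**
- Reconcile the ultrasound *and/or* with the screening definition of sonographic inflammation, stating which reading applies.
- Report the two parts of the endoscopic remission definition separately.

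**Weeks 52/60 maintenance comparison**
- Do not restrict. Patients in remission at re-randomisation are part of the question, so adjust for status at re-randomisation.

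**Cost.** A few lines of text and no new data. Denominators become smaller and differ by endpoint, and the restricted analysis may lose power if FMT works mainly by preventing worsening. The article does not say whether allocation precedes the week 0 endoscopy, so the subset should be justified by measurement before the first dose under blinding, not by a claim that it was made before randomisation.

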### Study design

The study design is detailed in figure 1.

**Figure 1 F1:**
[figure not shown]
Microbial Restoration study design. CDAI, Crohn’s Disease Activity Index; CRP, C reactive protein; FMT, faecal microbiota transplantation.

### Optimisation phase

Prior to randomisation, both study arms will be prescribed a course of antibiotic therapy, in addition to recommended dietary modification.

#### Antibiotic administration

All patients receive at day −10, for 7 days, a course of antibiotics comprising amoxycillin with clavulanic acid, metronidazole and norfloxacin (dosages: 1 g per oral two times per day; 400 mg per oral two times per day; and 400 mg per oral two times per day, respectively). Antibiotics cease 3 days prior to FMT or placebo administration.

#### Dietary modification

All patients will see a dietitian at study entry. Patients will be provided with detailed information on dietary modification to be commenced at study entry, 3 weeks prior to FMT or placebo administration, and continued throughout the study. The diet is a plant-enriched, whole-food approach that is free of food additives. Written dietary recommendations and suggested meal options and recipes are included on the MIRO study phone app.

### Induction phase

Patients assigned to receive upper gastrointestinal delivery of FMT will undergo endoscopic administration of FMT or placebo into the distal duodenum or jejunum at weeks 0, 2 and 6.

Patients receiving lower gastrointestinal delivery will undergo endoscopic administration of FMT or placebo into the ileum or right colon at week 0, followed by weekly FMT or placebo enemas until week 8.

At the week 8 assessment table 2, patients achieving a clinical response to FMT (CDAI decrease of ≥100 points or CDAI <150) enter the maintenance phase. Patients who achieve a partial response to FMT (CDAI decrease of <100 and >70 points) will be offered open-label extension of FMT for a further 8 weeks; if they fail to achieve complete clinical response to FMT at week 16, they will exit the study. Patients receiving initial (induction) placebo will be offered 8 weeks of open-label induction active FMT therapy; if they fail to achieve complete clinical response to FMT at week 16, they will exit the study. Patients receiving placebo therapy who achieve a clinical response at week 8 will exit the study.

**Table 2 T2:** Clinical outcomes assessments

	Method of assessment	Timepoints
Disease activity	Crohn’s Disease Activity Index	Weeks 0, 2, 6, 8 (±16), 16 (or 24), 24 (or 32), 32 (or 40), 40 (or 48), 48 (or 56), 52 (or 60)
Biomarkers	Blood: C-reactive protein	Weeks 0, 2, 6, 8 (±16), 16 (or 24), 24 (or 32), 32 (or 40), 40 (or 48), 48 (or 56), 52 (or 60)
	Stool: calprotectin	Weeks 0, 2, 8 (±16), 24 (or 32), 52 (or 60)
Sonographic assessment	IUS BWT <3 mm and/or Limberg Score 0 or 1; MRI BWT <4 mm and no/minimal wall enhancement	Weeks −3, 8 (±16), 52 (or 60)
Quality of life measures	Short-IBD-Q and EuroQol (EQ5D)	Weeks −3, 8 (±16), 52 (or 60)
Psychological assessment	Hospital Anxiety and Depression Scale (HADS)	Weeks −3, 8 (±16), 52 (or 60)
Endoscopy assessment	SES-CD	Weeks 0, 8 (±16), 52 (or 60)
Histological assessment	Presence of acute inflammation; Robarts Histology Index	Weeks 0, 8 (±16), 52 (or 60)
Diet tolerability	24-hour diet recall; Diet compliance assessment; Food additive survey	Weeks −3, 0, 8 (±16), 52 (or 60)
Safety	Surveillance	Duration of trial and up to 5 years following withdrawal/exit

BWT, bowel wall thickness; SES-CD, simplified endoscopic activity score for Crohn's disease.

### Open-label phase

The open-label therapy is administered according to the same schedule assigned to the patients in the induction phase. After 8 weeks of open-label FMT, patients will have another disease activity assessment; patients achieving a clinical response (CDAI decrease of ≥100 points or CDAI <150) from screening to end week 16 will enter the maintenance study.

### Maintenance phase

Patients who have had a clinical response at week 8 (or week 16 for those who received open-label FMT extension) will enter the maintenance study and will be re-randomised 1:1 to receive either active FMT or placebo for the remaining 44 weeks. Patients receiving upper gastrointestinal delivery will undergo endoscopic administration of FMT into the duodenum or jejunum every 8 weeks for 44 weeks. Patients receiving lower gastrointestinal delivery will undergo FMT enemas every 4 weeks for 44 weeks. At the week 52 assessment, or week 60 for those who received open-label FMT extension, the patients and study team will remain blinded.

Biological specimens will be collected in line with the study protocol and standard study procedures.

### Interventions

#### Treatment arm

##### Infusion product

The FMT product comprises whole stool prepared anaerobically and frozen. The frozen product will be thawed at room temperature for 4 hours prior to administration.

The administered FMT comprises 25% faecal material by weight, 65% normal saline and 10% glycerol.

##### FMT dose

FMT dose is 12.5 g of stool per 50 mL syringe.

Upper gastrointestinal delivery group: endoscopic administration of (25 g) 100 mL of FMT or placebo at each procedure (total induction dose: 75 g; total maintenance dose: 125 g).

Lower gastrointestinal delivery group: endoscopic administration of (50 g) 200 mL of FMT, followed by 100 mL of FMT or placebo enemas (total induction dose: 225 g; total maintenance dose: 250 g).

### Control arm

#### Placebo product

The placebo product contains 0.05% brown dye (combination mixture of HT Brown and Brilliant Blue FCF) in 0.9% normal saline and 10% glycerol. The product has been developed to be identical in appearance to FMT. Odourant is not used in this study as it is not able to be used according to Australian regulatory TGA guidelines.

### Preservation of double blinding

The participants, clinicians, research team and outcome assessors will be blinded to treatment allocation. The placebo product, packaging and labelling will be identical in appearance to the FMT product. The barcode numbers are indistinguishable between placebo and FMT products. The placebo product is frozen, stored and handled identically to the FMT product at each hospital site to prevent unblinding of study investigators during retrieval.

Unblinding will take place the day prior to the week 8 assessment of the induction phase to allow preparation of FMT or placebo for the open-label phase as FMT or placebo endoscopic infusion requires 4 hours of thawing. This unblinding will be undertaken by a designated team member who is not involved in the clinical running of the trial; they will allocate the maintenance syringe kit number. The study assessment, including IUS and endoscopy, will be performed by a study member who remains blinded to the treatment arm. In the event that a patient needs to be unblinded for medical care, a 24-hour contact number is available for immediate unblinding.

### Additional therapies

#### Metoclopramide

Intravenous metoclopramide 10 mg will be administered at the time of sedation by the anaesthetist to reduce the risk of aspiration through its antiemetic and prokinetic properties.

#### Loperamide

For patients with an ileorectal or ileosigmoid anastomosis, a dose of 4 mg or 2 mg of loperamide will be administered an hour prior to FMT administration via colonoscopy or enema, respectively, to maximise exposure of the FMT prior to defecation post-FMT.

#### Concomitant Crohn’s disease therapies

Patients will continue stable doses of their prestudy Crohn’s disease therapies, except for rectal therapies, which are not permitted due to the risk of trauma and potential subsequent bacteria translocation. Stable doses for 2 months prior to the study are required for immunomodulators and biologic agents, 1 month for small molecule inhibitors and 2 weeks for aminosalicylates.

#### Corticosteroid use

Participants can enter the study on prednisolone 20 mg or below, or budesonide 6 mg or below. However, mandatory corticosteroid tapering will be required from week 0 of 2.5 mg of prednisolone per week or 3 mg of budesonide every 2 weeks to ensure that participants do not remain on corticosteroids at the primary endpoint assessment.

Commencement of corticosteroid therapy after study entry will be considered a protocol deviation. However, patients can remain in the study unless it occurs within 4 weeks of the primary endpoint assessment, or if greater than two courses of more than 1 month duration are required during the entire study, either of which would be considered a protocol violation warranting withdrawal.

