#### Exclusion criteria

Exclusion criteria include active perianal or fistulising disease; pregnant or intending to become pregnant within 12 months; enteropathy or colitis other than Crohn’s disease; symptomatic intestinal stricture likely to require surgical or endoscopic treatment; presence of a stoma; presence of an ileoanal pouch; total white cell count less than 3.0×10^9^/L; albumin less than 20 g/L; immunodeficiency (beyond that caused by immunosuppressants used for the treatment of IBD) for example, HIV or common variable immune deficiency; anaphylaxis/severe allergy to food; thiopurine, methotrexate or biologic agent whose dose has been modified within the past 2 months; small molecule inhibitors whose dose has been modified within 1 month; aminosalicylates use within 2 weeks of study entry; prebiotic, probiotic or antibiotic therapy, or over-the-counter supplement therapy in the 2 weeks prior to study entry; rectal topical Crohn’s disease therapy in the 2 weeks prior to study entry; prednisolone dose >20 mg or budesonide dose >6 mg; unwilling or unable to taper corticosteroids to zero within 8 weeks of initial FMT; active gastrointestinal infection; alcohol consumption of a dependent nature; primary sclerosing cholangitis; any condition that the treating gastroenterologist deems to pose a theoretical risk to the patient undertaking FMT; any patient that the treating clinicians feel is incapable of participating in the safe use of FMT.

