### Early discontinuation/withdrawal/treatment failure

Patients may be withdrawn from the study if any of the following occurs:

The patient requests withdrawal from the study.Fails to attend one of the major study visits.Treatment failure, defined as:Clinical recurrence: symptoms typical of Crohn’s disease, necessitating unscheduled endoscopic or surgical intervention or addition of new drug therapy, associated with confirmed active disease.Failed corticosteroid withdrawal.Serious adverse events or complications necessitating cessation of therapy.Pregnancy.The investigator can also decide to withdraw a patient from the study if he/she considers it as necessary (eg, subsequent non-respect of inclusion criteria, a change in diagnosis).

At the time of withdrawal/discontinuation, patients will undergo a disease activity assessment including CRP, calprotectin, sonographic and endoscopic assessment if possible.

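### Aminosalicylate users are both excluded and admitted, early steroid starts are classified in two ways, and a CDAI-only primary endpoint counts a response on new steroids

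*Protocol article*

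**What the plan says.** **Aminosalicylates.** The Exclusion criteria section of the protocol article lists "aminosalicylates use within 2 weeks of study entry". The items beside it for thiopurines, methotrexate, biologics and small molecules exclude only a recent dose change; this one excludes use. The section on concomitant Crohn's disease therapies keeps patients on stable prestudy treatment, rectal therapy apart, and sets the required stable period at "1 month for small molecule inhibitors and 2 weeks for aminosalicylates".

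**New corticosteroids.** The Corticosteroid use section treats any steroid begun after entry as a deviation from the protocol, and adds that "patients can remain in the study unless it occurs within 4 weeks of the primary endpoint assessment". A second ground for withdrawal is a need for three or more courses that each last over a month. The same section tapers steroids present at entry "to ensure that participants do not remain on corticosteroids at the primary endpoint assessment". The section on early discontinuation and treatment failure makes typical Crohn's symptoms that lead to "addition of new drug therapy, associated with confirmed active disease" a treatment failure. It also lists failed corticosteroid withdrawal. Withdrawal there is optional.

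**Endpoint and analysis.** Table 1 and the Statistical analysis section define the primary endpoint as a CDAI fall of at least 100 points, or a CDAI below 150, at week 8. Neither adds a condition on steroids or new therapy. The primary set is every randomised patient who received at least one dose. The only steroid-free endpoint is secondary and is assessed at week 52 or 60.

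**The concern.** There are three separate problems.

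1. The aminosalicylate rules cannot both be applied to a patient on a stable oral dose. One site could enrol a patient whom the other site excludes, or the same patient could later be called an eligibility violation. That can affect who enters the per-protocol analysis.
2. A steroid started early for a confirmed flare is a protocol deviation with retention in one section and a treatment failure in another.
3. Whichever label applies, nothing in the article removes such a patient from the responder count if the week-8 CDAI is low enough. The trial would then credit the randomised arm with a response that came on rescue steroids. If rescue is commoner on placebo, the placebo rate rises more and a true FMT effect is diluted.

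**Working it through.** **Step 1: aminosalicylates.** Take a patient on an unchanged oral aminosalicylate dose for more than 2 weeks before entry. Under Exclusion criteria there was use within 2 weeks, so the patient is excluded. Under the concomitant-therapy section the dose was stable for 2 weeks, so the patient is admitted and continues. Rectal treatment does not explain the difference, because the exclusion list has its own item for it.

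**Step 2: the steroid window.** The deviation rule runs from study entry, which the Dietary modification section places 3 weeks before the first FMT or placebo dose (week −3). Starts within 4 weeks of the week-8 assessment warrant withdrawal, so the window for retention closes at 8 − 4 = week 4. The overlap therefore covers about week −3 to week 4.

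**Step 3: still on steroids at week 8?** Up to two courses longer than 1 month do not trigger withdrawal. One month is about 52/12 = 4.3 weeks. A course of that length begun just before week 4 ends after week 8, so a retained patient can be scored while still taking it.

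**Step 4: scoring.** The patient was randomised and dosed, so is in the primary set. The week-8 CDAI is observed and the definition uses CDAI alone. A sufficient fall is therefore a response. No sentence in the article makes treatment failure or new steroid use a non-response.

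**Step 5: the plan's own sample size.** Inputs from the Sample size, Randomisation and Discussion sections: 30% v 60%, 2:1 allocation, two-sided 0.05, 80% power, 20% dropout. With a pooled variance and p̄ = (0.30 + 2 × 0.60)/3 = 0.50,

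n(placebo) = [1.96·√(0.25 × 1.5) + 0.842·√(0.30 × 0.70 + 0.60 × 0.40/2)]² / 0.30² = (1.200 + 0.483)² / 0.09 = 31.5, rounded up to 32.

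The total is 32 + 64 = 96, and 96/0.8 = 120. Both stated figures reproduce.

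Power = Φ[(d − 1.96·SE₀)/SE₁], where SE₀ uses the pooled rate and SE₁ the separate rates: Φ[(0.30 − 1.96 × 0.1083)/0.1016] = 80.6%.

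**Step 6: illustration.** Assume that a share s of an arm starts steroids in the window, that these patients would otherwise be non-responders, and that a share r of them reaches CDAI response. The observed rate is then p + s·r. For example, with s = 10% on placebo and 5% on FMT and r = 0.5, the rates are 0.30 + 0.05 = 35% and 0.60 + 0.025 = 62.5%. All rows use 32 v 64 patients; s and r are assumptions.

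| s placebo / FMT | r | Placebo v FMT | Difference (points) | Risk ratio | Power |
|---|---|---|---|---|---|
| 0 / 0 | – | 30% v 60% | 30 | 2.00 | 81% |
| 5% / 2.5% | 0.5 | 32.5% v 61.25% | 28.75 | 1.88 | 77% |
| 10% / 5% | 0.5 | 35% v 62.5% | 27.5 | 1.79 | 73% |
| 20% / 10% | 1.0 | 50% v 70% | 20 | 1.40 | 48% |
| 5% / 5% | 0.5 | 32.5% v 62.5% | 30 | 1.92 | 80% |
| 20% / 20% | 1.0 | 50% v 80% | 30 | 1.60 | 85% |

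**The case against.** The strongest reply is that the steroid rules do not contradict each other. One calls the start a deviation and lets the patient stay; the other calls it treatment failure and makes withdrawal optional, and only where Crohn's symptoms and confirmed active disease are present. An investigator can obey both. This stands: a reader might infer that new steroids are simply allowed in one place and forbidden in another, and the text does not say that. What remains is one event with two labels.

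A reader might also infer that the overlap is what makes a steroid response count as a primary response. It is not. Both rules concern retention, and reconciling them would leave the scoring unchanged; the scoring follows from the CDAI-only endpoint. Nor is the aim "to ensure that participants do not remain on corticosteroids at the primary endpoint assessment" a rule on new courses, since it is attached to the taper of entry steroids.

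A third reply is that the analysis plan, which is not shown, may deal with this. The Statistical analysis section does say that its missing-data approach will vary with the kind of intercurrent event. But a rescued patient who attends week 8 has no missing CDAI, so that sentence does not clearly reach the case. The article itself fixes the endpoint, the analysis set and the retention rule, and together they produce a responder.

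Finally, the power figures depend on assumed rates, an assumed placebo excess and 96 evaluable patients. That is right. With all 120 evaluable (40 v 80), planned power is 89%, which leaves more room.

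**Conclusion.** The aminosalicylate conflict holds in full. It acts before randomisation, so it bears on eligibility and possibly the per-protocol set, and it does not by itself bias the comparison between arms.

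The steroid point holds in limited form. Between study entry and about week 4, a start for confirmed active disease is classified in two overlapping ways. Separately, the endpoint as written counts a retained patient's CDAI fall on new steroids as a response, possibly while the course is still running.

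No definite loss of power can be claimed, because the documents give no rescue rate. Under the assumptions shown, use twice as common on placebo lowers power from 81% to between 77% and 48%. Equal use leaves power at 80% to 85% but moves the risk ratio, which is the reported estimate, from 2.00 to between 1.92 and 1.60. The direction of the bias depends on how use differs between arms.

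**What to change.** **Analysis.** In the primary analysis, score as a week-8 non-responder any patient who, after study entry and before the week-8 CDAI, starts or increases corticosteroids for Crohn's disease or meets the article's treatment-failure definition. Report CDAI response regardless of rescue as a sensitivity analysis. Counting from study entry covers starts during the 3-week optimisation phase, and limiting the rule to Crohn's disease avoids penalising steroids given for another reason.

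**Text.** The investigators should reconcile the Exclusion criteria with the concomitant-therapy section on aminosalicylates, and the Corticosteroid use section with the treatment-failure section on new steroids. No clinical rule is proposed here.

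**Cost.** A change to the endpoint wording and a clarification to both sites. Response rates will be slightly lower in both arms. No extra visits or measurements are needed, but the start date, any dose increase and the reason for steroid use must be recorded.
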